#### Withdrawals and loss to follow-up

Dyads can withdraw from the study at any time. The ‘intention-to-treat’ principle will apply for participants who withdraw or are lost to follow-up.

#### Independent data and safety monitoring committee (IDSMC)

The IDSMC monitors SAE reports throughout the trial, and oversees trial progress, ensuring that it is conducted, recorded, and reported in accordance with the protocol, good clinical practice, and applicable regulatory requirements. The IDSMC provides recommendations about stopping or continuing the trial in the event of harm, undue risks, or futility. IDSMC members (Appendix 1) met (via teleconference) prior to the start of enrolment. Subsequent IDMSC teleconferences are scheduled every four months, and at trial termination, or more frequently as necessary.

#### Sample size

The sample size was based on previous data for SEIQoL-DW [15] and POS-S-MS [8]; for both outcomes we considered changes at three months compared to baseline.

SEIQoL-DW: a sample size of 21 patients assigned to HPA (study intervention) and 11 assigned to UC (control) has a power of 80% to detect an assumed mean change of score of 31.5 (standard deviation (SD) 12.8) in the HPA group compared to a change of 12.1 (SD 19.3) (null hypothesis) in the UC group, at alpha level 0.05 using a two-sided, two-sample *t* test. Assuming 20% dropout, 25 patients are required in the HPA group and 13 in the UC group (total sample size 38).

POS-S-MS: a sample size of 41 HPA and 21 UC has a power of 85% to detect an assumed mean change of −0.4 (SD 0.5) in the HPA group, with a concomitant change of 0.2 (SD 0.8) (null hypothesis) in the UC group; assuming an alpha level of 0.05 and a two-sided, two-sample *t* test. Assuming 20% dropout, 49 patients are required in the HPA group and 25 patients in the UC group (total sample size 74).

It is expected that up to 50% of MS patients have severe cognitive compromise, and will not be able to complete SEIQoL-DW, in these the only primary endpoint will be the POS-S-MS. We aim to recruit 50 patients in the HPA group and 25 patients in the UC group, thereby achieving an exact 2:1 ratio of intervention to control.

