### Limitations and concerns

We estimated a sample size of 75 patients, which is rather small for a phase II/III trial. We based our sample size estimate on published data: for POS-S-MS, these data come from MS patients with similar characteristics to our study population [8], and for SEIQoL-DW, from people with severe MS or other neurodegenerative conditions [15]. In view of our limited sample size, we used adaptive (minimization) randomization to ensure comparability of study arms.

Another limitation is that, in contrast with previous trials [8,15], our trial did not originate from palliative services, which in theory can directly address needs identified. Our HPA aims to activate existing services or bring them to the attention of the dyad. The extent to which these aims are achieved cannot be predicted.

Finally, having a blind examiner renders trial procedures considerably more complex: the blind examiner must have no contact with the HPA team; dyads must be briefed about the importance of keeping the examiner blinded; and, prior to three- and six-month visits, the blind examiner is instructed to caution dyads against disclosing their assignment or mentioning issues related to study procedures. In addition, costs and intensity of care outcomes, as assessed by the MSCQ, are assessed by telephone interviews at three and six months conducted by an independent professional - again to prevent examiner unmasking.

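### The 20% dropout allowance multiplies by 1.2 where it should divide by 0.8, so the stated 74 and 38 do not keep the evaluable numbers; a minor error that restated figures correct

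*Protocol article*

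**What the plan says.** All of this stands in the protocol article under Sample size.

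- **SEIQoL-DW.** The plan says "a sample size of 21 patients assigned to HPA (study intervention) and 11 assigned to UC (control) has a power of 80" (per cent). The mean changes behind this are 31.5 (SD 12.8) for HPA and 12.1 (SD 19.3) for UC. The dropout step follows: "Assuming 20% dropout, 25 patients are required in the HPA group and 13 in the UC group (total sample size 38".
- **POS-S-MS.** 41 HPA and 21 UC patients are said to give 85% power for mean changes of −0.4 (SD 0.5) and 0.2 (SD 0.8). Then: "Assuming 20% dropout, 49 patients are required in the HPA group and 25 patients in the UC group (total sample size 74".
- **Test.** Both calculations use a two-sided two-sample t test at alpha 0.05, on change from baseline to three months.
- **Target.** Recruitment is set at 50 HPA and 25 UC, and the reason given is an exact 2:1 ratio. Up to half the patients are expected to be unable to complete SEIQoL-DW.

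Limitations and concerns repeats the total: "We estimated a sample size of 75 patients, which is rather small for a phase II/III trial".

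**The concern.** The figures after dropout are presented as what is required if 20% of patients are lost. If they are right, removing 20% should return the evaluable numbers. It does not: 80% of 49 is 39.2, not 41, and 80% of 25 is 20, not 21. The same failure occurs for SEIQoL-DW.

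Both primary outcomes are affected, and the stated powers of 85% and 80% are then not what the plan's own dropout assumption delivers. UC is the smaller arm with the larger SD for both outcomes, so losses there weigh most on the standard error.

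**Working it through.** **Inputs** (all from Sample size): evaluable numbers 41/21 and 21/11 (HPA/UC); dropout 20%; target 50/25; differences in mean change of 0.2 − (−0.4) = 0.6 for POS-S-MS and 31.5 − 12.1 = 19.4 for SEIQoL-DW; SDs 0.5 and 0.8, and 12.8 and 19.3; two-sided alpha 0.05.

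**1. The evaluable numbers reproduce.** Power was computed from the noncentral t distribution, with SE = √(SD₁²/n₁ + SD₂²/n₂) and Satterthwaite degrees of freedom.

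- POS-S-MS, 41/21: SE = √(0.25/41 + 0.64/21) = 0.191; 0.6/SE = 3.14; power 85.7% (stated 85%).
- SEIQoL-DW, 21/11: SE = √(163.84/21 + 372.49/11) = 6.45; 19.4/SE = 3.01; power 80.1% (stated 80%).

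Pooled-SD versions of the test do not reproduce the stated powers, so the unequal-variance form is used throughout. The fault is confined to the dropout step.

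**2. The dropout step.**

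| Outcome, arm | Evaluable n | n × 1.2 | Stated | n / 0.8 | Rounded up | Left from stated figure after 20% loss |
|---|---|---|---|---|---|---|
| POS-S-MS, HPA | 41 | 49.2 | 49 | 51.25 | 52 | 39.2 |
| POS-S-MS, UC | 21 | 25.2 | 25 | 26.25 | 27 | 20.0 |
| SEIQoL-DW, HPA | 21 | 25.2 | 25 | 26.25 | 27 | 20.0 |
| SEIQoL-DW, UC | 11 | 13.2 | 13 | 13.75 | 14 | 10.4 |

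Multiplying by 1.2 and rounding gives all four stated figures. Dividing by 0.8 gives 52 + 27 = 79 and 27 + 14 = 41. Inflating the totals instead gives 62/0.8 = 77.5, so 78, and 32/0.8 = 40. The stated totals cover losses of 1 − 62/74 = 16.2% and 1 − 32/38 = 15.8%.

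**3. What the target of 75 delivers for POS-S-MS.** 50 × 0.8 = 40 and 25 × 0.8 = 20. Power at 40/20 is 84.0%. The shortfall is one patient in each arm.

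**4. What the target of 75 delivers for SEIQoL-DW.** This depends on how many patients cannot complete the instrument. With 2:1 allocation and 20% dropout among those who can:

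| Unable to complete | Able, of 75 | Completers (HPA/UC) | Power |
|---|---|---|---|
| 50% | 37.5 | 20/10 | 75.9% |
| 45% | 41.25 | 22/11 | 80.4% |
| 40% | 45 | 24/12 | 84.1% |

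From the stated 25/13, 20% loss leaves 20/10.4 and about 77.5% power if the fraction is kept.

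**5. How much dropout each stated power tolerates.**

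- POS-S-MS from 50/25: the total of 62 is kept up to (75 − 62)/75 = 17.3% loss, and 85% power holds to just under 18%.
- SEIQoL-DW from 25/13: 80% power holds to about 15.5%; at 17% it is 79.3%.
- SEIQoL-DW from 75 enrolled with half unable to complete (25/12.5): 80% power holds to about 12%; at 17% it is about 77.7%.

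**The case against.** The strongest reply is that little depends on the error. POS-S-MS sets the size of the trial, and recruitment is 50/25, not 49/25. After 20% loss the trial is one patient short per arm, and power falls one point below the stated 85%. That stands, and it is why the point is minor. It does not make the stated requirement correct: the target was rounded to get an exact 2:1 ratio, and the UC arm stays at 25.

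A second reply is that the intention-to-treat analysis uses linear mixed models and multiple imputation (Statistical analyses), so patients who drop out may still contribute information. That is fair as far as it goes, and the powers given here are those of a completers' t test. But the Sample size section uses that same t test with its own dropout allowance and claims no recovery from modelling.

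A third reply concerns SEIQoL-DW. The 50% is given as an upper limit, so 76% power is the figure at that limit and not what the trial will deliver in general. This stands, and any statement of that power needs the condition attached.

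A reader might also infer that the original powers hold for both outcomes up to about 17% dropout, because 75 falls to 62 at 17.3%. The figures do not support this: it is true of POS-S-MS only.

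**Conclusion.** The dropout arithmetic is wrong as written for both primary outcomes, and nothing elsewhere in the article corrects it. The stated totals are short by 4 to 5 patients for POS-S-MS (74 against 78 or 79) and by 2 to 3 for SEIQoL-DW (38 against 40 or 41). At 20% dropout the target of 75 gives about 84% power for POS-S-MS. For SEIQoL-DW it gives about 76% if half the patients cannot complete the instrument, and at least 80% if about 45% or fewer cannot.

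This is a minor correction. A reader might infer that the trial is seriously underpowered or must recruit more. The article's figures do not show that: the loss is one point for the outcome that fixes the sample size, and about four points for the other only at the limit of its assumption.

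The powers rest on the plan's means and SDs, an unequal-variance t test, equal dropout in both arms and, for SEIQoL-DW, the 2:1 ratio holding among patients able to complete it.

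**What to change.** In Sample size:

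- Replace 49/25 (74) by 52/27 (79), and 25/13 (38) by 27/14 (41), as the numbers that 20% dropout requires. If the totals are inflated instead, give 78 and 40 and say so.
- Keep 75 (50/25) as the target. State that it is slightly below the corrected requirement and that 20% dropout leaves 40/20 and about 84% power for POS-S-MS under the t-test assumptions.
- For SEIQoL-DW, state that about 20/10 completers and 76% power remain if 50% cannot complete it, and that 80% is still reached if about 45% or fewer cannot.
- If a tolerable dropout rate is quoted, limit the figure of about 17% to POS-S-MS. For SEIQoL-DW the limits are about 15.5% from 25/13, and about 12% from 75 enrolled with half unable to complete.

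The total of 75 in Limitations and concerns can stay. The cost is slightly less favourable stated figures, with no extra patients and no change of design.

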**Methods/design:**

This is a single-blind randomized controlled trial with a nested qualitative study. Seventy-five severe MS-carer dyads are being randomized (at three centers, one in each area of Italy) to HPA or usual care (UC) in a 2:1 ratio. Each center has a specially trained team consisting of four professionals (physician, nurse, psychologist, social worker). The team makes a comprehensive assessment of the needs of the dyads. HPA content is then agreed on, discussed with the patient’s caring physician, and delivered over six months. The intervention is not intended to replace existing services. At later visits, the team checks the HPA delivery and reviews/modifies it as necessary.

HPA and UC dyads are assessed at home by a blind examiner at baseline, and three and six months later; they also receive monthly telephone interviews. Dyads assigned to UC receive the examiner’s visits and telephone interviews, but not the team visits.

Primary outcome measures are changes in symptoms (Palliative care Outcome Scale-Symptoms-MS, POS-S-MS), and quality of life (the Schedule for the Evaluation of Individual Quality of Life-Direct Weighting (SEIQoL-DW), not assessed in patients with severe cognitive compromise) at three and six months. Other outcomes are changes in patient functional status and mood; changes in carer quality of life, mood and caregiving burden; costs; incorporation with standard care; unplanned hospital admissions; referrals to hospice; and deaths.

The experience of participants will be evaluated qualitatively by individual semi-structured interviews (HPA patients and carers) and focus group meetings (HPA patients’ caring physicians).

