#### Inclusion and exclusion criteria

All adults (18 years or older) who fulfill all the following criteria are potentially eligible:Diagnosis of MS [18]Expanded Disability Status Scale (EDSS) ≥8.0 [19]Primary or secondary progressive coursePresence of a carer (family member, relative, or friend, who is next of kin or is key decision maker as designated by the (cognitively competent) MS patient and with whom the patient shares his/her life)At least two unmet care needs among the categories identified in the PeNSAMI Phase 1 qualitative study (Table 1) [11], or the patient declares for comfort care only

**Table 1 Tab1:** **List of main care need categories, as identified in the PeNSAMI Phase 1 qualitative study** [11]

**Domain**	**Category**
**‘** ***Managing everyday life*** **’**	Symptoms management
	Personal care/hygiene
	Activities of daily living
	Outdoor mobility and transport
**‘** ***Psychosocial*** **’**	Relationships/communication
	Leisure/holidays
	Psychological well-being/social role
**‘** ***Organization*** **’**	Information
	Access to services
	Co-ordination of services
	Competent professionalsOne or more of the following: significant complex symptoms/medical complications, dysphagia/poor nutritional status, communication difficulties [20].

Exclusion criteria are:Hospitalized/institutionalized patientsPatients already receiving palliative careDyads living out of study area

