**Table 2 Tab2:** **Outcome measures and timing of follow-up**

	**Baseline**	**Three-month follow-up**	**Six-month follow-up**
General characteristics	X	X	X
MS history	X	X	X
Medical history	X	X	X
EDSS	X	X	X
FIM	X	X	X
SEIQoL-DW^*^	X	X	X
Core-POS^**^	X	X	X
POS-S-MS^**^	X	X	X
HADS^*^	X	X	X
EQ-5D^*^	X	X	X
MSCQ	X	†	†
Carer characteristics /medical history	X	X	X
Carer HADS	X	X	X
Carer SF-36	X	X	X
Carer EQ-5D	X	X	X
Carer ZBI	X	X	X

To preserve blinding, all outcome measures (except MSCQ) are assessed during examiner visits at three and six months follow-up. ^*^Not assessed in MS patients with severe cognitive compromise or unable to communicate; ^**^carer versions used in MS patients with severe cognitive compromise or unable to communicate; ^†^assessed by phone interview. Core-POS, Core-Palliative care Outcome Scale; EDSS, Expanded Disability Status Scale; EQ-5D, European Quality of Life Five Dimensions; FIM, Functional Independence Measure; HADS, Hospital Anxiety and Depression Scale; MSCQ, Multiple Sclerosis foundation Costs Questionnaire; MS, multiple sclerosis; POS-S-MS, Palliative care Outcome Scale-Symptoms-Multiple Sclerosis; SF-36, Short Form 36; SEIQoL-DW, Schedule for the Evaluation of Individual Quality of Life-Direct Weighting; ZBI, Zarit Burden Interview.

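### At the protocol's own 50% limit on non-completion, 75 randomised patients give SEIQoL-DW about 76% power rather than 80%, with no reserve for the further exclusion in Table 2

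*Protocol article*

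**What the plan says.** SEIQoL-DW is one of two primary outcomes. On its size, the Sample size section of the protocol article says: "a sample size of 21 patients assigned to HPA (study intervention) and 11 assigned to UC (control) has a power of 80" (per cent). The inputs behind that figure are three-month changes averaging 31.5 (SD 12.8) under HPA and 12.1 (SD 19.3) under UC, compared by an unpaired t test, two-sided at the 5% level. With 20% dropout the requirement becomes 25 HPA and 13 UC, 38 in total. The recruitment target, 50 HPA and 25 UC, follows from the other primary outcome, POS-S-MS.

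The same section then says "It is expected that up to 50% of MS patients have severe cognitive compromise, and will not be able to complete SEIQoL-DW", and that POS-S-MS is the only primary endpoint in those patients.

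The rule on who is not assessed appears in two forms:
- **Cognitive status only.** The Abstract (Methods/design) describes SEIQoL-DW as "not assessed in patients with severe cognitive compromise) at three and six months". The Sample size section uses the same single reason. The Primary outcomes section likewise names only severe cognitive impairment as the reason for not completing questionnaires.
- **Cognitive status or communication.** The Table 2 footnote that applies to SEIQoL-DW reads "Not assessed in MS patients with severe cognitive compromise or unable to communicate".

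The inclusion criteria ask for at least one feature from this list: "significant complex symptoms/medical complications, dysphagia/poor nutritional status, communication difficulties".

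**The concern.** The number recruited looks comfortable for SEIQoL-DW (75 against 38) until the 50% figure is applied. It then falls half a patient short, and the dropout allowance behind the 38 is itself too small. With nothing in reserve, it matters that Table 2 removes a further category of patient that the sizing leaves out.

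Two things are at stake. If non-completion reaches the planning limit, a null SEIQoL-DW result could be read as coming from an 80%-powered comparison when the design did not provide one. And with two versions of the non-assessment rule, centres could differ on which patients contribute to a primary outcome.

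**Working it through.** **Inputs (Sample size section unless noted).** Mean changes 31.5 and 12.1, so the difference is 19.4. SDs 12.8 (HPA) and 19.3 (UC). Two-sided alpha 0.05. Evaluable 21/11. Dropout 20%. Randomised 50/25. Up to 50% unable to complete SEIQoL-DW. The share unable to communicate but without severe cognitive compromise is not given anywhere.

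**Step 1: reproduce the stated power.** Unequal-variance two-sample t test:
- SE = √(12.8²/n₁ + 19.3²/n₂)
- Noncentrality = 19.4/SE
- Satterthwaite degrees of freedom, power from the noncentral t distribution

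At 21/11: SE = √(7.80 + 33.86) = 6.455, noncentrality 3.01, df 14.7, power **80.1%**. The stated 80% is reproduced. The same method gives 85.7% for POS-S-MS at 41/21, where the protocol states 85%. This is therefore the most plausible method behind both figures.

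**Step 2: check the dropout step.**
- Multiplying: 21 × 1.2 = 25.2 and 11 × 1.2 = 13.2, which match the stated 25/13.
- If 20% of 25/13 are lost, 25 × 0.8 = 20 and 13 × 0.8 = 10.4 remain, short of 21/11.
- Dividing: 21/0.8 = 26.25 and 11/0.8 = 13.75, rounded up to **27/14**.

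**Step 3: apply the 50% figure to 75 randomised.** 50 × 0.5 = 25 and 25 × 0.5 = 12.5, total 37.5 against 38. After 20% dropout: 20/10. SE = √(8.19 + 37.25) = 6.741, noncentrality 2.88, df 13.1, power **75.9%**.

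**Step 4: vary total non-completion for any reason, with 20% dropout throughout.**

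| Assessable | At entry (HPA/UC) | Evaluable (HPA/UC) | Power |
|---|---|---|---|
| 60% | 30/15 | 24/12 | 84.1% |
| 55% | 27.5/13.75 | 22/11 | 80.4% |
| 50% | 25/12.5 | 20/10 | 75.9% |
| 45% | 22.5/11.25 | 18/9 | 70.6% |
| 40% | 20/10 | 16/8 | 64.3% |

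The last two rows correspond to 5 or 10 percentage points of patients unable to communicate, added without overlap to 50% with severe cognitive compromise. Both increments are assumptions. Any other route to the same total gives the same power.

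**Step 5: break-even.** 80% power survives up to about 45% total non-completion. In whole patients the UC arm is limiting: 14 of 25 must be assessable, so at most 11 of 25 (44%) may be non-completers. On the protocol's own 13, the limit is 12 of 25 (48%).

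**The case against.** The strongest objection is that the protocol says up to 50%, which is an upper bound and not an expected rate. If 40% have severe cognitive compromise and a further 5 points cannot communicate, 22/11 remain and power is still 80.4%. This stands: the documents do not show that a shortfall will occur.

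A reader might also infer that the communication exclusion is what takes SEIQoL-DW below 80%, and that its true power is 64 to 76%. The documents support neither inference. The shortfall that can be computed from the protocol's own figures appears with no communication exclusions at all; it comes from the 50% limit together with the dropout step. The size of the communication group and its overlap with cognitive compromise are unknown. Having communication difficulties, one of several alternative entry features, is not the same as being unable to communicate. The criterion makes an empty group unlikely but says nothing about its size.

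It can be said that the protocol attaches 80% to 21/11 evaluable patients, and that this is correct. That also stands. The problem is that 75 randomised do not yield 21/11 at the protocol's own limit.

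The Abstract and Sample size wording may be shorthand for the fuller rule in Table 2. If so, the sizing text still counts only one of the two reasons.

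Finally, a t calculation with an n-weighted pooled SD stays above 80% down to 16/8 (80.6%). But it gives 91.0% at 21/11, so it is not the calculation behind the stated 80%. The planned mixed model could also change realised power, but the protocol's claim rests on a t test of the three-month change.

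**Conclusion.** The point holds as a conditional one. At the protocol's upper planning figure of 50% non-completion and its own 20% dropout, 75 randomised give about 20/10 evaluable and about 76% power, roughly 4 percentage points below the stated 80%. Part of this comes from inflating 21/11 to 25/13 instead of 27/14. There is no reserve at 50%, while Table 2 excludes a further group that the sizing does not count. Any loss beyond 76% depends on that group's size and overlap, which the protocol does not give. Power of 80% remains attainable if total non-completion is about 45% or less.

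This rests on the protocol's assumed means and SDs, the unequal-variance t test that reproduces its figures, and dropout at the same rate in both arms and among assessable patients.

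**What to change.** 1. Use one SEIQoL-DW non-assessment rule, determined at baseline, in the Abstract, Primary outcomes, Table 2 footnote and Sample size section.
2. Correct the dropout-inflated SEIQoL-DW requirement from 25/13 to 27/14.
3. State the expected total share unable to complete SEIQoL-DW for any reason, in place of the share with severe cognitive compromise alone.
4. Give SEIQoL-DW power for 75 randomised over a range that includes favourable cases: about 84%, 80%, 76%, 71% and 64% at 60%, 55%, 50%, 45% and 40% assessable. Keep 80% only as the power at 21/11 evaluable.

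The cost is wording and a less favourable stated power for one primary outcome. This change needs no extra patients.

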#### Statistical analyses

Continuous data will be summarized using means, medians, SDs, minimums and maximums. Between-group comparisons will employ either the two-sided unpaired *t* test or Wilcoxon’s two-sided two-sample test for non-normal data. Distributions will be tested for normality using the Shapiro-Wilk test. Correlations will be estimated using Spearman’s or Pearson’s coefficients. Categorical data will be compared by χ2 or Fisher’s exact test.

Longitudinal changes in SEIQoL-DW and POS-S-MS will be analyzed using linear mixed models for longitudinal data [48,49]. All tests will be two-tailed. *P* values <0.05 will be considered significant. For the primary intention-to-treat analyses, multiple imputation of missing values will employ Rubin’s approach. The analyses will be performed with Stata Statistical Software, release 12 (StataCorp LP, College Station, TX, USA), or SAS, release 9.2 (SAS Institute Inc., Cary, NC, USA).

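### The sample size relies on unequal SDs, larger in the smaller arm, but the analysis section does not carry this over; if the usual pooled-variance forms are used, type I error is about 8.4–9.1% for the t test

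*Protocol article*

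**What the plan says.** The Sample size section gives arm-specific SDs for the three-month change in each primary outcome. For SEIQoL-DW it assumes a "mean change of score of 31.5 (standard deviation (SD) 12.8) in the HPA group compared to a change of 12.1 (SD 19.3") in usual care (UC), with "a sample size of 21 patients assigned to HPA (study intervention) and 11 assigned to UC (control"), and states that this "has a power of 80% to detect an assumed mean change of score". For POS-S-MS the assumed changes are −0.4 ("SD 0.5) in the HPA group, with a concomitant change of 0.2 (SD 0.8") in UC, with 41 HPA and 21 UC patients and 85% power. The test is given for SEIQoL-DW as "at alpha level 0.05 using a two-sided, two-sample" t test, and likewise for POS-S-MS. The recruitment target is 50 and 25, exactly 2:1.

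The Statistical analyses section reads "Between-group comparisons will employ either the two-sided unpaired" t test or, for non-normal data, Wilcoxon's test. For the primary outcomes it adds: "Longitudinal changes in SEIQoL-DW and POS-S-MS will be analyzed using linear mixed models for longitudinal data". Two-tailed P "values <0.05 will be considered significant". Nothing there says whether variances are pooled or allowed to differ between arms, for either the t test or the mixed model.

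**The concern.** Unequal allocation with the larger variance in the smaller arm is the configuration in which pooling does harm. The pooled variance is weighted towards the larger, less variable arm, so the standard error of the difference comes out too small. P values are then too low and intervals too narrow. The planning figures put both primary outcomes in this configuration, with SD ratios (UC over HPA) of 19.3/12.8 = 1.51 and 0.8/0.5 = 1.6. The analysis section leaves open a choice that the sample size had already made. The ordinary forms of both named methods assume a common variance, so an analyst following the article could depart from the planning assumption without noticing. After dropout UC would have about 20 patients for POS-S-MS and perhaps about 10 for SEIQoL-DW, so the choice could decide whether a result is called significant.

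**Working it through.** **Inputs** (Sample size section): SEIQoL-DW difference 31.5 − 12.1 = 19.4, SDs 12.8 and 19.3, n 21 and 11. POS-S-MS difference 0.2 − (−0.4) = 0.6, SDs 0.5 and 0.8, n 41 and 21. Two-sided alpha 0.05.

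**1. Reproducing the stated power.** Separate-variance SE = √(s₁²/n₁ + s₂²/n₂), Satterthwaite degrees of freedom, noncentral t.

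- SEIQoL-DW: √(163.84/21 + 372.49/11) = √(7.80 + 33.86) = 6.45; df 14.7; noncentrality 19.4/6.45 = 3.01; power 80.1%.
- POS-S-MS: √(0.25/41 + 0.64/21) = √(0.00610 + 0.03048) = 0.191; df 28.2; noncentrality 0.6/0.191 = 3.14; power 85.7%.

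These match the stated 80% and 85%. The other forms tried do not match both:

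| Form | SEIQoL-DW | POS-S-MS |
|---|---|---|
| Pooled t, formula treating the pooled SD as common | 91.0% | 94.6% |
| Pooled t, simulated with the planned SDs | 88.2% | 91.9% |
| Unpooled normal approximation | 85.2% | 88.0% |
| Larger SD in both arms, noncentral t | 74.3% | 78.5% |
| Larger SD in both arms, normal approximation | 77.1% | 79.8% |

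**2. What pooling does to the SE.** Pooled variance = [(n₁−1)s₁² + (n₂−1)s₂²]/(n₁+n₂−2).

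- SEIQoL-DW: (20×163.84 + 10×372.49)/30 = 233.4; SE = √233.4 × √(1/21 + 1/11) = 15.28 × 0.372 = 5.69, against a true 6.45. Ratio 0.881.
- POS-S-MS: (40×0.25 + 20×0.64)/60 = 0.38; SE = 0.616 × 0.268 = 0.165, against a true 0.191. Ratio 0.865.

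The SE is understated by about 12% and 14%. The large-sample type I error is 2Φ(−1.96 × ratio): 2Φ(−1.727) = 8.4% and 2Φ(−1.695) = 9.0%.

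**3. Simulated type I error** (normal data, equal means, planned SDs, 400,000 trials per setting for the t tests):

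| Setting | Pooled t | Welch t |
|---|---|---|
| SEIQoL-DW 21/11 | 8.4% | 5.1% |
| SEIQoL-DW 25/13 | 8.5% | 5.1% |
| POS-S-MS 41/21 | 9.0% | 5.0% |
| POS-S-MS 50/25 | 9.1% | 5.0% |

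Pooled 95% intervals cover about 91% (POS-S-MS) to 92% (SEIQoL-DW), whatever the true difference in means. Wilcoxon gives about 6.4–7.4%, so the fallback for non-normal data is not a full remedy.

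**4. Mixed model with a common variance.**

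- Unstructured covariance common to both arms, complete data: the three-month contrast has the same estimate and SE as the pooled t test, so 8.4–9.0%.
- Random intercept on the two change scores: 7.5–9.6%.
- Random intercept on three visits: 6.7–11.8% as the correlation between the two changes runs from 0.3 to 0.7; at 0.5 it is 8.3–9.3%. This correlation is an assumption, as the article gives none.

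Multiple imputation, which the plan also names, was not modelled.

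**5. Dependence on the SD ratio** (pooled t, POS-S-MS sizes 41/21): 5.0% at ratio 1.0, about 6.4% at 1.2, 7.8% at 1.4 and 9.0% at 1.6.

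**The case against.** The tempting stronger reading is that the analyses named in the article themselves run at 8–9% type I error. The text does not support that, for four reasons.

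- "Unpaired" means independent groups. Welch's test is unpaired too, and the article nowhere says pooled or common variance. The only place where the variance form can be inferred, the power calculation, points to unequal variances. Read consistently with it, the t test holds 5%.
- Residual covariance structure and degrees-of-freedom method for a mixed model are details that an article usually leaves to the full protocol or analysis plan, which may well specify them. Their absence is not in itself an error.
- There is no single error rate for "the" mixed model. It varies with structure and with a correlation not given.
- The SDs are planning values from earlier trials in which the mean changes also differed. Type I error concerns equal means, and if the arms then share an SD, pooling holds 5%.

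All four stand, and they make the point conditional. They do not remove it: the sample size depends on an assumption that the analysis section does not repeat, and the ordinary form of each named method drops it. The last reason does not touch interval coverage, which depends on the SDs and not on the means being equal.

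**Conclusion.** The point holds as a conditional one. The power figures rest on unequal variances, and the analysis section leaves the variance assumption open. With a pooled t test and SDs as planned, type I error is about 8.4–9.1%, against 5.0–5.1% for Welch. A common-variance mixed model, the analysis named for both primary outcomes, falls in the range of about 7–12%. These figures assume normal data, the planned SDs holding under the null, and, for the mixed model, complete data with a correlation of 0.3 to 0.7 between changes. A smaller SD ratio gives a smaller effect, down to none at equal SDs. This is a free improvement to the plan. It does not show that the trial will be analysed wrongly.

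**What to change.** State in the Statistical analyses section, or in the analysis plan before outcome data are seen by arm, that between-group t tests use the unequal-variance (Welch/Satterthwaite) form that the sample size already implies. For the primary mixed models, specify arm-specific residual variances with Satterthwaite or Kenward-Roger degrees of freedom, and confirm that the chosen software release provides them.

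The cost is one sentence and a model option. Intervals will be slightly wider than pooled ones if the SDs differ as planned, and the model carries a few more variance parameters, which matters somewhat with a small UC arm. No patients are added, and power stays at the stated level (80.1% and 85.7% by the t test calculation), because that calculation already uses the separate-variance SE.
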